## Abstract

**Background:**

Postoperative wound infection is a preventable risk. One potential postoperative complication is blistering, which leads to increased pain, delayed healing, and higher care costs. The incidence of wound blisters has been reported to be between 6 and 24%. The aim of this study is to assess whether the risks of postoperative blistering and wound infections within the first 6 days postsurgery will be reduced using a special dressing compared to a standard one.

**Methods/Design:**

This is a randomized clinical trial in a University hospital. Patients presenting for knee or hip arthroplasty or spine procedures will be assessed against study inclusion and exclusion criteria. After giving written informed consent, patients will be randomized to participate in the 7-day study during hospitalization. One hundred patients will be randomized per group. The primary outcome measure is blistering incidence from day 0 to day 6 postsurgery. Photo documentation will be evaluated in a blinded manner by the Clinical Evaluation Committee (CEC).

**Discussion:**

A new dressing will be compared to the standard wound dressing regarding the risk of postoperative blistering, wound infection, and patient comfort. This study will assess the potential advantages of a modern wound dressing.

**Trial registration:**

ClinicalTrials.gov identifier NCT01988818 (Entered 13 November 2011).

## Background

In view of an increasing elderly population, several authors expect further increases of joint replacement and spine procedures in western industrialized nations [1-3]. One postoperative complication is wound blistering, which leads to increased pain, delayed healing, and increased susceptibility to wound infection due to compromised skin integrity. Blistering occurs when the dermis is separated from the epidermis, and is the invariable result of continuous abrasion. The deep, finger-like projections of epidermal tissue holding the epidermis and dermis together are weakened, allowing the two skin layers to separate. Most blistering occurs on the fifth or sixth postoperative day [4].

There are several other factors that influence the development of blistering. These include the skin changes generally evident in older patients: that is, there is less production of collagen (a tough, fibrous protein that makes skin strong) and elastin (which makes skin flexible). Collagen production decreases significantly with age after the fifth decade [5].

The Incidence of wound blistering has been reported in the literature to be between 6 and 24% [4,6,7]. Postoperative wound complications and surgical site infections can increase recovery times, inpatient care costs, and morbidity rates [8].

Mepilex^®^ Border Post-Op is a highly conformable self-adherent dressing that absorbs blood exudates and should minimize the risk of maceration. The adhesive uses Safetac^TM^ technology, a unique and patented soft silicone adhesive technology that is designed to minimize pain as well as trauma to the wound and surrounding skin. Mepilex Border Post-Op is CE marked on the equivalent device Mepilex^®^ Boarder.

In a recent randomized clinical study, three types of dressings (Mepore Pro, Mepilex Border, and Hypafix Transparent) were compared in 150 consecutive hip surgery subjects regarding the occurrence of tape blisters. Blister prevalence was significantly lower for the Mepilex Border group (3%) than for the Mepore Pro (59%, *P* <0.01) and Hypafix group (61%, *P* <0.01). The mean time between surgery and blister occurrence and the total number of dressings used during hospital stay were also significantly lower for the Mepilex Border group compared to the Mepore Pro and Hypafix groups (*P* <0.01). In summary, the dressing with a silicone adhesive (Mepilex Border) significantly reduced the prevalence of blisters following hip surgery [9].

The overall rationale for the current trial is to evaluate the clinical performance of Mepilex Border Post-Op regarding the risks of blistering and maceration as well as the need for dressing changes, due to its high absorptive capacity compared to standard wound dressings. In addition, its performance after spine surgery will be evaluated. To our knowledge, it is the first randomized clinical trial with modern wound dressings for spine surgery at this stage of development.

### Objective

The primary objective of this clinical trial is to evaluate the performance of a self-adhesive absorbent postoperative dressing coated with a soft silicone layer in minimizing the risk of blistering compared to the hospital standard dressing (Cosmopor E^TM^, Fa. Hartmann) after hip and knee arthroplasty or spinal surgery. The study will be conducted in a clinical care setting at a University Hospital. Secondary objectives are to evaluate dressing performance, comfort, conformability and overall acceptability, pain before, during, and after dressing removal, overall cost regarding dressing wear time, time for dressing changes, and required personnel resources. Wound blisters will be documented by photographing and counting the number of blisters and its size. The documentation is done by one member of our Clinical Evaluation Committee (CEC) during the whole period of the study. The evaluation will be done separately by different members of our CEC in a blinded manner.

## Methods/Design

The study is designed as a randomized trial in a clinical care setting at a University hospital with two parallel groups. Patients presenting for knee or hip arthroplasty or spine surgery will be assessed according to study inclusion and exclusion criteria. Hip and knee arthroplasty are often done in standardized operation procedures. In spine surgery, there is a large variety of operations. We decide to standardize this by excluding operations with a hospital stay of fewer than 6 days, infections, tumor operations or revisions in general. After written informed consent, the patients will be randomized to participate in the 7-day study. The research in this trial will be performed with the approval of the Ethics Committee of the Medical Faculty of the University Hospital of Cologne under the reference number 13-348. The study is performed monocentrally, so there is no other Ethics Committee involved. Research carried out in the trial will be in compliance with the Helsinki Declaration.

### Participants and recruitment

Patients aged 18 years or older presenting for hip or knee arthroplasty or spine surgery and who will stay longer than 6 days in-house, are eligible for the trial. Patients whose wounds cannot be appropriately covered with the dressing will be excluded from this study.

Inclusion criteria are as follow:Age ≥18 yearsAn expected total length of inpatient stay of 6 or more daysUndergoing elective primary arthroplasty of the hip or knee or spinal surgeryUndergoing hip surgery with a standard approachWritten informed consent to participate

Exclusion criteria are as follow:Sized dressings that are not appropriate for the incision/woundKnown allergy/hypersensitivity to any dressing componentsPolytrauma patientsUndergoing arthroplasty due to tumorFracturesWound at the surgical site prior to surgeryNeurological deficit of operated side (hemiplegia, *etcetera*)Subject has documented skin disease at time of enrolment, as judged by the investigator

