### Intervention

The patients will be randomized 1:1 preoperatively as either the Mepilex Border Post-Op group or the standard dressing group (Figure 1). The Mepilex Border Post-Op group will get the first dressing removal 6 days after surgery. The standard wound dressing group will receive dressing removals at day 2, 4 and 6 postsurgery. Both groups will be visited every day postsurgery to allow evaluation and documentation of the appearance of the dressing.

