### Outcome measures and assessments

The primary outcome measure is blistering incidence from day 0 to day 6 postsurgery. Photo documentation will be evaluated in a blinded manner by the CEC. The secondary objectives will evaluate the dressing performance, comfort and overall acceptability by standardized assessment criteria. The individual pain before, during and after the dressing removal will be documented in a 1 to 10 rating scale equal to the visual analog scale. During the removal of the dressing, we will count the used materials and keep records of the time spent in minutes to summarize the resources and costs in general.

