### Statistical analysis

Primary analysis will be according to the intention-to-treat. A patient is evaluable for this analysis if they underwent surgery and received a study treatment. If the clinical course cannot be fully evaluated, the patient will be considered a treatment failure. Secondary analysis will include all patients essentially treated and observed according to protocol (per protocol set, PPS), that is, no study visit missed, key outcome variables taken.

Primary outcome analysis: The proportion of incident blistering in the two groups will be compared with a two-sided type I error of 5% by the Mantel-Haenszel test, stratified by type of surgery: that is, the null hypothesis H_0_: common odds ratio for blistering = 1 is tested against the alternative hypothesis H_A_: common odds ratio for blistering ≠ 1. A subgroup analysis by type of surgery and gender will be performed. Heterogeneity of treatment effect and 95% confidence intervals (odds ratio, relative risk, and risk difference) will be evaluated by Mantel-Haenszel methods.

Secondary outcome analysis: Pain, number of dressing changes/blisters, and performance/acceptability ratings will be analyzed by rank-based methods, that is, Wilcoxon rank sum/signed rank test. Other wound complications will be assessed by chi-square test (or Fisher’s exact test when required).

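### The two length-of-stay criteria conflict and neither is counted from surgery, so a patient can be eligible yet leave before the postoperative day-6 assessment that completes the primary endpoint

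*Protocol article*

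**What the plan says.** The protocol article sets the required stay in three places.

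- Participants and recruitment, opening sentence: patients "who will stay longer than 6 days in-house, are eligible for the trial".
- Participants and recruitment, inclusion list: an "expected total length of inpatient stay of 6 or more" days.
- Methods/Design, on standardizing spine surgery: "excluding operations with a hospital stay of fewer than 6 days".

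The endpoint and its assessments are counted from surgery. Under Outcome measures and assessments: "The primary outcome measure is blistering incidence from day 0 to day 6 postsurgery". Under Intervention, for the test arm: "The Mepilex Border Post-Op group will get the first dressing removal 6 days after surgery"; for the control arm: "The standard wound dressing group will receive dressing removals at day 2, 4 and 6 postsurgery". The same section has both groups visited daily to document the appearance of the dressing. The abstract places the whole observation in hospital: "patients will be randomized to participate in the 7-day study during hospitalization".

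For incomplete observation, Statistical analysis states: "If the clinical course cannot be fully evaluated, the patient will be considered a treatment failure". The Sample size section expects no loss to follow-up and randomizes 100 per group against a calculated 93.

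**The concern.** An eligibility rule based on length of stay is there to ensure that the patient is still present when the endpoint is completed. This one does not do so reliably, for two reasons.

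First, a patient with an expected stay of exactly 6 days is ineligible under the opening sentence and eligible under the inclusion list. Second, both statements count time in hospital, whereas the endpoint counts time since surgery. A night in hospital before the operation uses up part of the required stay without adding to postoperative observation.

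The days at risk are the important ones. The Background puts most blistering on the fifth or sixth postoperative day. The arms also differ in what an early departure loses. A control patient leaving on day 5 would have had scheduled removals on days 2 and 4; a test patient would have had none. In the primary analysis such a patient is not set aside as missing but counted as a failure. That raises the event rate in both arms and pulls the odds ratio, the parameter tested, towards 1.

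**Working it through.** **Step 1. Do the criteria agree?** Take an expected stay of exactly 6 days.

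| Statement | 6-day stay |
|---|---|
| Participants and recruitment, opening sentence | not eligible |
| Participants and recruitment, inclusion list | eligible |
| Methods/Design, spine surgery | not excluded |

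The Methods/Design statement agrees with the inclusion list. The conflict is between the opening sentence and the other two.

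**Step 2. Which postoperative day does the stay reach?** Let L be the total stay and a the number of days from admission to surgery (0 or 1; an assumption, since the article does not give the admission day). Surgery is day 0.

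- If L counts nights, discharge falls on day L − a.
- If L counts calendar days, discharge falls on day L − a − 1.

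| Counting | Admission | L = 6 | L = 7 (shortest whole-day stay longer than 6) |
|---|---|---|---|
| nights | day of surgery | day 6 | day 7 |
| nights | day before | day 5 | day 6 |
| calendar days | day of surgery | day 5 | day 6 |
| calendar days | day before | day 4 | day 5 |

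A 6-day stay ends before day 6 in three of the four cases, and a 7-day stay in one of the four. Choosing the stricter wording therefore reduces the problem but does not remove it.

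**Step 3. Reproduce the plan's sample size.** Inputs from Sample size: 17.7% and 4.8%, 80% power, two-sided 5%, uncorrected chi-square test. With mean rate (0.177 + 0.048)/2 = 0.1125:

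n = [1.960·√(2·0.1125·0.8875) + 0.8416·√(0.177·0.823 + 0.048·0.952)]² / 0.129²
= [0.8758 + 0.3682]² / 0.01664 = 93 per group.

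This matches the stated 93. At 100 per group, z = (10·0.129 − 0.8758)/0.4375 = 0.947, so power is 82.8%.

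**Step 4. What would the failure rule do?** Suppose a share m of each arm is scored as failure, independently of blistering. The expected rate becomes p* = m + (1 − m)p. For example, m = 5% gives 0.05 + 0.95·0.177 = 0.218 and 0.05 + 0.95·0.048 = 0.096. The values of m are assumed; the article gives none.

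| m in each arm | Control | Test | Odds ratio | Power at 100 per group | n per group for 80% |
|---|---|---|---|---|---|
| 0 | 17.7% | 4.8% | 4.27 | 82.8% | 93 |
| 2% | 19.3% | 6.7% | 3.34 | 76.1% | 111 |
| 5% | 21.8% | 9.6% | 2.64 | 66.6% | 138 |
| 10% | 25.9% | 14.3% | 2.09 | 53.5% | 187 |

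At m = 2%, that is 2 of 100 patients per arm, the required number (111) already exceeds the 100 randomized.

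**The case against.** The strongest reply is that the text permits early leavers but does not show that there will be any. The criterion is a minimum, and most patients may stay well beyond it. The article gives no admission day, counting convention or distribution of stay; it describes a 7-day in-hospital study, and the investigators expect no loss. All of that stands. A reader might infer that patients due to leave early are in fact being enrolled and scored as failures; the document does not support that.

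Three other strong readings also go too far.

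- That a patient with a 6-day stay cannot supply the endpoint. If nights are counted and admission is on the day of surgery, discharge falls on day 6 and the assessment is possible.
- That the skin of a test-arm patient who leaves early would never have been inspected. Visits are daily, and the description of the test dressing gives it a transparent adhesive section. The visits document the dressing and the area over the wound is white, so this is not a full inspection, but it is not nothing. What can be said is that no dressing removal is scheduled before day 6 in that arm.
- That all three stay statements conflict. Two of them agree.

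It is also fair to say that the power figures do not measure this defect alone. They come from the failure rule, which applies to any patient who cannot be evaluated, whatever the cause, and they rest on assumed shares. With equal shares in both arms, they do not measure the difference in lost information between arms either. Finally, the article does not expressly equate treatment failure with a blister, although for a binary primary outcome that is the natural reading.

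None of this resolves the conflict between the two criteria or supplies the missing link to surgery. The conflict is in the published text, so it is not a detail left to a fuller protocol.

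**Conclusion.** The point holds as a defect of wording that bears on the primary endpoint. Participants and recruitment contains two incompatible thresholds, and none of the stay statements is anchored to the date of surgery. Under three of the four plausible conventions for admission and counting, the looser threshold admits a patient who leaves on postoperative day 4 or 5. The stricter one does so under one of the four, with departure on day 5. Such a patient would enter the primary analysis as a failure, in a trial sized for no loss.

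The size of the effect cannot be determined from the document. The illustrative power of about 76%, 67% or 54% assumes that 2%, 5% or 10% of each arm is affected, equally in both arms and independently of blistering, that failure means a blister, and that the planned rates of 17.7% and 4.8% are right. It uses the unstratified chi-square approximation of the plan's own sample size rather than the stratified Mantel-Haenszel test. It shows how little loss the design tolerates; it does not predict the loss.

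**What to change.** Reconcile the stay statements in Methods/Design and in Participants and recruitment into one criterion tied to the endpoint: expected to remain in hospital through the postoperative day-6 assessment. This removes the need to define how days are counted or when patients are admitted. Add that photographs from any dressing removal that happens before day 6 are sent to the CEC for blinded evaluation, so that whatever was observed is on record when the failure rule is applied.

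The change is one eligibility sentence and one documentation sentence, by amendment. The article states that enrolment was under way at submission, so the amendment should come promptly. The cost is that a few short-stay patients become ineligible and recruitment may be slightly slower. The criterion still rests on an expected stay, so an unforeseen early discharge remains possible and would still fall under the failure rule.

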### Intervention

The patients will be randomized 1:1 preoperatively as either the Mepilex Border Post-Op group or the standard dressing group (Figure 1). The Mepilex Border Post-Op group will get the first dressing removal 6 days after surgery. The standard wound dressing group will receive dressing removals at day 2, 4 and 6 postsurgery. Both groups will be visited every day postsurgery to allow evaluation and documentation of the appearance of the dressing.

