### Randomization

Patients will be randomly assigned to one of the two treatment groups (allocation ratio 1:1). The randomization will be stratified according to surgery type (hip, knee, or spine) and blocked (permuted blocks of varying length). The randomization will be implemented by sequentially numbered, opaque, sealed envelopes containing details of the dressing to be applied.

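### The primary set called intention-to-treat can lose a randomised, operated patient who receives neither study dressing, and one exclusion depends on a surgical wound that does not yet exist at preoperative randomisation

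*Protocol article*

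**What the plan says.** Four statements in the protocol article bear on this.

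- **Timing (Intervention):** "The patients will be randomized 1:1 preoperatively as either the Mepilex Border Post-Op group or the standard dressing group". Methods/Design has eligibility assessed first and then: "After written informed consent, the patients will be randomized to participate in the 7-day study".
- **Mechanism (Randomization):** "sequentially numbered, opaque, sealed envelopes containing details of the dressing to be applied". The article does not say when the envelope is opened or by whom. Blinding is described only for the evaluation: "Photo documentation will be evaluated in a blinded manner by the CEC".
- **Exclusion (Participants and recruitment):** "Patients whose wounds cannot be appropriately covered with the dressing will be excluded from this study". The exclusion list repeats the idea as a mismatch between dressing size and incision or wound. Neither place gives a time point. A wound already present at the site is a separate exclusion, so the wound meant here is the surgical one.
- **Primary set (Statistical analysis):** "Primary analysis will be according to the intention-to-treat", followed by "A patient is evaluable for this analysis if they underwent surgery and received a study treatment" and "If the clinical course cannot be fully evaluated, the patient will be considered a treatment failure". A per-protocol set is defined separately.

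**The concern.** Randomisation protects the comparison only if patients stay in the analysis regardless of what happens after allocation. Here, membership of the primary set depends on receiving a dressing, which comes after allocation. Fit to the wound, one reason a dressing might not be applied, is also named as a ground for exclusion, and the article sets no rule for a patient already randomised whose wound proves unsuitable.

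Once an envelope is open, staff know the arm, because the products look different and have different removal schedules. If removals then differed between arms and fell on wounds more prone to blistering, the blister rates would differ without any product effect. Calling the set intention-to-treat would tell readers that this cannot happen.

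**Working it through.** **1. The plan's own figure.** Inputs (Sample size section): p1 = 0.177, p2 = 0.048, two-sided 5%, 80% power, uncorrected chi-square test.

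n = [1.960·√(2·p̄·(1−p̄)) + 0.842·√(p1(1−p1) + p2(1−p2))]² / (p1−p2)², with p̄ = 0.1125.

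- 1.960·√0.1997 = 0.876
- 0.842·√0.1914 = 0.368
- (0.876 + 0.368)² / 0.129² ≈ 93 per group, as stated

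Power is 80.0% at 93 and 82.8% at 100 per group. The sample size is correct and is not at issue.

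**2. Who leaves the primary set, on the wording.**

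| Randomised patient | Had surgery | Received a study treatment | In primary set? | Arm stated? |
|---|---|---|---|---|
| Allocated dressing applied | yes | yes | yes | not in doubt |
| Other study dressing applied | yes | yes | yes | no |
| Neither study dressing applied | yes | no | no | – |
| Surgery cancelled | no | no | no | – |

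The third row is the problem and the second is an ambiguity. The treatment-failure sentence follows the evaluability condition and does not clearly bring the third row back.

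**3. How large a bias could be.** The article gives no exclusion rate, so everything here is assumed. Suppose there is no true effect (17.7% in both arms). From one arm only, x of 100 patients are removed, with blister risk m times the average. The risk among those left is

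k = 0.177·(100 − x·m)/(100 − x).

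For example, x = 10 and m = 3 gives 0.177·70/90 = 0.1377, a difference of −3.9 points. Type I error is by exact enumeration of the unstratified uncorrected chi-square test, 100 against 100 − x patients. It approximates the planned stratified Mantel-Haenszel test.

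| Removed (x) | Risk multiple (m) | Remaining risk | Apparent difference (points) | Odds ratio | Type I error |
|---|---|---|---|---|---|
| 0 | – | 17.7% | 0 | 1.00 | 5.1% |
| 2 | 2 | 17.3% | −0.4 | 0.98 | 5.1% |
| 2 | 3 | 17.0% | −0.7 | 0.95 | 5.2% |
| 5 | 2 | 16.8% | −0.9 | 0.94 | 5.3% |
| 5 | 3 | 15.8% | −1.9 | 0.87 | 6.4% |
| 10 | 2 | 15.7% | −2.0 | 0.87 | 6.5% |
| 10 | 3 | 13.8% | −3.9 | 0.74 | 11.3% |

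Removals at average risk (m = 1) cause no bias, and type I error stays at about 5%. If the planned 4.8% held in the new-dressing arm, the same formula would shift that rate by 0.1 points (0.048·96/98 = 0.0470) to 1.1 points (0.048·70/90 = 0.0373).

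**4. What the handling of these patients does to power.** If removals are equal in both arms and unrelated to risk, power is 80.8% at 95 and 78.7% at 90 per group. If the patients are instead kept and all counted as failures, each arm's rate becomes (x + (100 − x)·p)/100. With 5 per arm, that is 21.8% against 9.6%. Power at 100 per group is then 76.1%, 66.6% or 53.5% for 2, 5 or 10 such patients per arm. Retaining them with their observed outcome avoids this loss.

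**The case against.** The strongest reply is that coverability is an ordinary eligibility criterion. Methods/Design puts screening before randomisation, arthroplasties are elective and primary, hips use a standard approach, and an incision can be planned. The list item speaks of dressings in the plural and names neither product. This stands in part. A reader might infer that coverability is known only at closure, that exclusions do occur after randomisation, or that fit is judged against the allocated product. The documents support none of these as fact. What remains is that the criterion is worded in terms of the wound, the final wound does not exist at randomisation, and Methods/Design itself notes the wide variety of spine operations.

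A reader might also infer that the surgeon knows the arm while making the incision and closing. Preoperative allocation makes this possible, but no envelope-opening time is given, and an article may leave that to the full protocol.

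One might further infer that difficult wounds are dropped from the new-dressing arm alone. The wording does not imply this: a patient switched to the other study dressing has still received a study treatment and stays in. No dressing sizes are given that would suggest a fit problem confined to one arm. The one-arm scenario above is therefore a worst case.

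Finally, the treatment-failure rule works against convenient removal, but only for patients who are in the set. Excluding patients who never had surgery is common practice, and the proposed set keeps that exclusion. Cancellation is unlikely to depend on which dressing was allocated, whereas receipt of a dressing may.

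**Conclusion.** The point holds in a limited form. As written, the primary set is conditional on treatment received and is not intention-to-treat, whenever coverability is judged. It can drop a randomised, operated patient after allocation, and it leaves open the arm of analysis for a patient given the other dressing. The wound-dependent exclusion, with randomisation before surgery, gives one concrete route by which this could happen.

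The size is unknown. Bias is negligible if exclusions are few or unrelated to blister risk. It matters only if they are frequent, differ by arm and carry higher risk. The 11.3% type I error needs all three at once: 10 of 100 patients, one arm only, triple risk. The documents neither support nor rule out such a rate. The case for changing the text is that the protection is cheap, not that bias has been shown.

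**What to change.** **Analysis set, for all patients including those already enrolled.** Define the primary set as every randomised patient who underwent surgery, analysed in the allocated arm whatever dressing was applied, with the observed blister outcome used wherever it was assessed. The treatment-failure rule then applies only where it was not. Move the requirement of having received a study treatment to the per-protocol set. Report post-randomisation exclusions by arm with reasons, including cancelled operations.

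**Procedure, for future patients.** Judge coverability against the available sizes of both dressings before the envelope is opened, preferably by opening it after skin closure. If this is already the practice, say so and correct the Intervention section.

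**Cost.** One or two sentences on the analysis set, a short amendment and an instruction to theatre staff. The envelopes already exist, and the 93 required and 100 randomised per group stay as they are. There is a small downside: the envelope is handled in theatre, and the procedure changes during enrolment (the trial was recruiting when the article was submitted). The change applies to both arms alike, so the comparison between arms remains randomised.

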### Mepilex Border Post-Op

Patients in this study group will receive postoperative wound treatment using the Mepilex Border Post-Op dressing (Mölnlycke, Goteborg, Sweden). This is a self-adhesive, absorbent dressing designed for acute wounds. It consists of three main parts. Firstly, there is a flexible and transparent backing film that is highly vapor permeable and waterproof: it is coated with a pressure sensitive water-based acrylic adhesive. Secondly there is a flexible, absorbent wound pad consisting of two layers: an absorbent layer with a perforated pattern for good flexibility, retention, and absorption capacity and a gap layer for high initial absorption and good distribution of exudates. Finally, it also includes a wound contact layer of acrylate adhesive, polyurethane film and soft silicone. The soft silicone layer adheres gently to dry skin surrounding the wound, but not to the moist wound surface. The soft silicone layer is covered with a polyethylene release film. The wound coverage section is white and the adhesive section is transparent to ease placement.

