## Discussion

Postoperative wound infection is a preventable risk associated with significant adverse outcomes and increased costs of care. Currently, patients are treated with a standard dressing, which is changed every 2 days. A comfortable wound dressing that minimizes the risk of blistering, which will be changed only after 7 days, once the wound edges have closed, could minimize the risks of postoperative superficial wound infections. Because both treatments are acceptable, we can compare them in an attempt to optimize postoperative wound care. Finally, not only the used dressing mentioned in this study can influence the outcome of developing wound blisters and complications. Also the number of dressing changes in general may have a significant influence on the outcome. This would be considered separately in the final examination of the study results.

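### Skin is scheduled to be uncovered three times in the standard arm but once in the Mepilex arm, so a cumulative day 0 to 6 blister endpoint can be biased towards Mepilex; the size is unknown and may be small

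*Protocol article*

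**What the plan says.** The endpoint is cumulative. Under Outcome measures and assessments: "The primary outcome measure is blistering incidence from day 0 to day 6 postsurgery".

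The removal schedule differs by arm. Under Intervention: "The Mepilex Border Post-Op group will get the first dressing removal 6 days after surgery", and "The standard wound dressing group will receive dressing removals at day 2, 4 and 6 postsurgery". Scheduled exposures of the skin within the outcome window are therefore one and three.

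The daily visits are the same in both arms, but their stated object is the dressing: "Both groups will be visited every day postsurgery to allow evaluation and documentation of the appearance of the dressing". The description of the Mepilex dressing adds that "The wound coverage section is white and the adhesive section is transparent to ease placement", so skin under the pad cannot be inspected before removal, though skin under the border might be.

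Blisters are photographed and counted, and the photographs are evaluated blind by the Clinical Evaluation Committee (CEC). The article does not give the days of photography, and does not say that the primary outcome rests on a look common to both arms.

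On timing, the Background says: "Most blistering occurs on the fifth or sixth postoperative day". The Discussion describes the Mepilex dressing as one "which will be changed only after 7 days, once the wound edges have closed", which differs from the timing under Intervention.

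**The concern.** A cumulative incidence is comparable between arms only if an event has the same chance of being found in each. Here a blister that forms by day 4 can be seen at a scheduled removal in the standard arm. In the Mepilex arm it must still be readable on day 6 to count, unless it is noticed through the transparent border. A blister that has collapsed, ruptured or healed by then would count in one arm and not in the other.

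Extra looks can only add detected cases, and the scheduled extra looks are all in the standard arm. Any bias from this source would therefore run towards Mepilex and would be read as a dressing effect. Blinded reading does not cure it, because blinding the reader does not equalise the number of looks.

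At stake is the type I error of the primary test and the size of the reported relative risk.

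**Working it through.** **1. The plan's own figure.** Inputs (Sample size): p1 = 0.177, p2 = 0.048, two-sided 5%, 80% power, uncorrected chi-square.

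n = [z0.975·√(2p̄(1−p̄)) + z0.80·√(p1(1−p1)+p2(1−p2))]² / (p1−p2)², with p̄ = (0.177+0.048)/2 = 0.1125.

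n = [1.960·√0.19969 + 0.8416·√0.19137]² / 0.129² = (0.8758 + 0.3682)² / 0.016641 = 93.0.

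The stated 93 per group reproduces. By the same normal approximation, power is 80.0% at 93 and 82.8% at 100 per group. Nothing below disputes the sample size.

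**2. Model for unequal detection.** Suppose the dressings are equal, with true incidence p in both arms. Let f be the share of all blisters that a day-2 or day-4 look finds but a single day-6 look does not. The standard arm then shows p, the Mepilex arm shows p(1−f), and the apparent relative risk is 1−f. The document does not give f, so it is an assumption shown over a range.

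**3. Type I error.** Exact binomial enumeration with n = 100 per arm, rejecting when |a−b| / √(2p̄(1−p̄)/n) > 1.96, where a and b are the observed proportions and p̄ their mean. This unstratified test approximates the planned stratified Mantel-Haenszel test. Results at p = 17.7%:

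| f | Mepilex arm shows | Apparent RR | Two-sided error | Of which favours Mepilex |
|---|---|---|---|---|
| 0 | 17.7% | 1.00 | 5.1% | 2.6% |
| 5% | 16.8% | 0.95 | 5.5% | 3.7% |
| 10% | 15.9% | 0.90 | 6.4% | 5.3% |
| 15% | 15.0% | 0.85 | 8.1% | 7.4% |
| 20% | 14.2% | 0.80 | 10.6% | 10.2% |
| 30% | 12.4% | 0.70 | 18.4% | 18.3% |

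At the ends of the incidence range in the Background, f = 20% gives 5.9% (incidence 6%) and 13.2% (incidence 24%).

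**4. Plausible f.** f is the share of blisters arising by day 4 multiplied by the share of those unreadable on day 6. If 30% arise early and half of those are unreadable, f = 0.30 × 0.50 = 15%. If most blisters arise on day 5 or 6, fewer than half arise by day 4. Then f = 30% needs more than 0.30/0.50 = 60% of early blisters to be unreadable on day 6.

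**5. Other routes.** If blisters persist but each look has a sensitivity of 0.7 to 0.9, with 10% to 50% arising early, the error is 5.1% to 7.3%. If each look adds 1% to 3% false-positive calls, it is 6.1% to 12.6%.

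**6. Power if day 6 were the primary endpoint, f = 20% in both arms.** The rates become 0.177 × 0.8 = 14.2% and 0.048 × 0.8 = 3.8%. Power at 100 per arm falls from 82.8% to about 73% by normal approximation (85.6% to 75.9% by exact enumeration). The formula in step 1 then gives about 120 per group for 80% power.

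**The case against.** The strongest reply is that the schedule makes bias possible without showing that it occurs. Both arms are uncovered on day 6. The Background puts most blistering on day 5 or 6 and links blisters to delayed healing, and nothing says that they vanish within days. If every early blister is still readable on day 6, f = 0 and the error is about 5%. This stands, and it is why no single figure can be given for the bias.

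The transparent Mepilex border may also let some early blisters be seen at the daily visits, while the standard dressing is described as nonwoven polyester with no mention of transparency. This stands in part: it could reduce f, and it means that the net direction is likely rather than certain. It does not help with skin under the white pad.

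The Discussion concedes that the number of dressing changes may influence the outcome and promises to consider it separately. That concerns an effect on the skin, not detection, and no method is given, so it does not answer the point.

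A reader might infer that the primary result is certain to be biased, or that the bias always favours Mepilex. The document supports neither, because f is unknown and the border is transparent. A reader might also infer that day-2 and day-4 photographs reveal allocation and so defeat the blinded reading. The article gives no photography days and does not say that readers receive a patient's full set, so this is a risk to close off and not an established fault.

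On removal timing, days 0 to 6 span seven calendar days and the article calls this a 7-day study, so the two statements may be loose descriptions of one schedule. The text does not settle it.

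**Conclusion.** The point holds as a risk that the plan leaves open. A cumulative day 0 to 6 endpoint is paired with three scheduled skin exposures in one arm and one in the other, and nothing in the article equalises detection. Bias, mainly towards Mepilex, follows if some blisters found on day 2 or 4 are missed on day 6.

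At the planning incidence of 17.7% the consequence ranges from none (f = 0) through slight (f = 10%) to a doubling of the nominal error (f = 20%) and more (f = 30%). At 6% incidence it is minor even at f = 20%. These figures assume equal dressings, 100 evaluable patients per arm and an unstratified approximation to the primary test. Given the stated timing of blisters, the lower values of f are the more plausible, but the document cannot fix the value.

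**What to change.** 1. State the days on which blisters are photographed and counted in each arm.
2. Pre-specify a key sensitivity analysis: the Mantel-Haenszel comparison, stratified by surgery type, of blister presence at the day-6 assessment after dressing removal in both arms. Report it beside the cumulative result, and interpret any superiority claim in its light.
3. For that analysis, give the blinded CEC the day-6 photographs without any day-2 or day-4 images.
4. Reconcile the Mepilex removal timing in Intervention (6 days after surgery) with that in the Discussion (after 7 days). If removal fell after day 6, the day-6 status under the dressing would not be observed in that arm.

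The cost is small: a paragraph of text and a separate day-6 read. Both arms have a removal scheduled on day 6 under Intervention, so the dressing schedule need not change.

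Making day-6 status the primary endpoint is an option for the investigators. It would equalise ascertainment, but it changes the question from incidence over the window to presence on day 6, drops early blisters that have resolved, and carries the power cost in step 6 of the working. It would therefore need a fresh look at the sample size. The sensitivity analysis addresses the detection question without that cost. Neither option separates the dressing from any effect of the removals themselves on the skin.
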